## Abstract

**Background:**

Most patients who suffer a stroke experience reduced walking competency and health-related quality of life (HRQoL). A key factor in effective stroke rehabilitation is intensive, task-specific training. Recent studies suggest that intensive, patient-tailored training can be organized as a circuit with a series of task-oriented workstations.

Primary aim of the FIT-Stroke trial is to evaluate the effects and cost-effectiveness of a structured, progressive task-oriented circuit class training (CCT) programme, compared to usual physiotherapeutic care during outpatient rehabilitation in a rehabilitation centre. The task-oriented CCT will be applied in groups of 4 to 6 patients. Outcome will be defined in terms of gait and gait-related ADLs after stroke. The trial will also investigate the generalizability of treatment effects of task-oriented CCT in terms of perceived fatigue, anxiety, depression and perceived HRQoL.

**Methods/design:**

The multicentre single-blinded randomized trial will include 220 stroke patients discharged to the community from inpatient rehabilitation, who are able to communicate and walk at least 10 m without physical, hands-on assistance. After discharge from inpatient rehabilitation, patients in the experimental group will receive task-oriented CCT two times a week for 12 weeks at the physiotherapy department of the rehabilitation centre. Control group patients will receive usual individual, face-to-face, physiotherapy. Costs will be evaluated by having each patient keep a cost diary for the first 24 weeks after randomisation. Primary outcomes are the mobility part of the Stroke Impact Scale (SIS-3.0) and the EuroQol. Secondary outcomes are the other domains of SIS-3.0, lower limb muscle strength, walking endurance, gait speed, balance, confidence not to fall, instrumental ADL, fatigue, anxiety, depression and HRQoL.

**Discussion:**

Based on assumptions about the effect of intensity of practice and specificity of treatment effects, FIT-Stroke will address two key aims. The first aim is to investigate the effects of task-oriented CCT on walking competency and HRQoL compared to usual face-to-face physiotherapy. The second aim is to reveal the cost-effectiveness of task-oriented CCT in the first 6 months post stroke. Both aims were recently recommended as priorities by the American Hearth Association and Stroke Council.

**Trial registration:**

This study is registered in the Dutch Trial Register as NTR1534.

## Background

The number of stroke patients is rising worldwide. The number in The Netherlands has been estimated at 7.5 per 1000, resulting in a prevalence of 118,500 in the year 2000[1]. Costs related to the care of stroke patients are extremely high and estimated to exceed one billion Euros in The Netherlands alone[2]. These numbers are expected to increase by 27% in 2020, due to improved health care and the ageing population[1].

Stroke patients experience lifetime disabilities and need care over a long period of time to cope with the consequences of their stroke. One study found that after rehabilitation, 62% of stroke patients were still dependent regarding daily living activities (ADL) and 32% were inactive regarding Instrumental ADLs at three years post stroke[3]. Moreover, about one fifth of chronic stroke patients suffer a significant decline in mobility[4], whereas less than 50% of patients manage to walk independently in the community again[5,6]. A qualitative study showed that loss of independent ambulation, especially outdoors, was one of the most disabling aspects for stroke patients[7]. Mobility-impaired patients are prone to inactivity and often have a sedentary lifestyle, which may result in a variety of problems including deteriorating gait, social isolation, feelings of depression and fatigue, ultimately affecting their quality of life[4]. In addition, reduced exercise tolerance as a result of inactivity may lead to secondary complications in stroke survivors, such as reduced cardio-respiratory fitness, muscle atrophy, osteoporosis and impaired circulation in the lower extremities[8]. Moreover, many patients with stroke suffer from diabetes mellitus, high blood pressure, body mass index above 30 and coronary heart disease, factors that in themselves increase the risk of other cardiovascular events, including recurrent strokes [9-11]. The lack of walking competency and physical fitness after stroke due to inactivity is of great concern to the health care system, as it is presumably associated with increasing costs[8].

A number of studies have shown that walking competency can be improved when practice is delivered in an intensive, and preferably task-oriented way [12-19]. For example, a meta-analysis of 13 RCTs (N = 501) showed that rehabilitation services in which the physical training is applied in a progressive and preferably task-oriented way are more effective than usual individual care, in terms of gait speed and walking distance[18]. Unfortunately, most stroke physiotherapists and occupational therapists are hampered in the implementation of intensive, task-oriented training by lack of time due to insufficient staff and inefficient use of human resources[20,21]. Group training, in which multiple patients practice meaningful tasks simultaneously, may be an effective method to overcome this problem. A recent meta-analysis showed that task-oriented circuit class training (CCT), in which training is organized as a circuit with a series of workstations, had positive effects in terms of gait speed, walking distance and the timed-get-up and go test, compared to usual care[19].

Task-oriented CCT generally seems to satisfy at least three key conditions for an effective and efficient physical training programme compared to usual face-to-face training. First, the use of different workstations in task-oriented CCT allows patients to practice intensively in a meaningful and progressive scheme suited to their individual needs. Second, task-oriented CCT might represent an efficient use of therapists' time while patients actively engage in task practice, compared to individual therapy. This makes circuit class training a potentially effective method which saves costs to the health care system by reducing staff-to-patient ratios. Third, task-oriented CCT involves group dynamics including peer support and social interaction[22].

Unfortunately, the literature offers only a few high-quality studies on the effectiveness of task-oriented CCT, whereas studies investigating its cost-effectiveness are still lacking[14,17,19]. The American Hearth Association recently emphasized the need for research to explore the health benefits and cost-effectiveness of structured exercise programmes to improve physical fitness in patients with stroke[8].

The study whose protocol is presented here intends to investigate the effectiveness and cost-effectiveness of task-oriented CCT programmes compared to usual face-to-face physiotherapy provided during outpatient physiotherapy treatment at a rehabilitation centre. We hypothesize that task-oriented CCT programmes will be a better strategy to improve functional outcome in patients discharged to the community from a rehabilitation centre than individual face-to-face training at the physiotherapy department of an outpatient rehabilitation clinic. In addition, based on the rules for reimbursement by insurance companies, we assume that training in groups will entail lower short-term and long-term costs to the health care system than face-to-face treatments applied individually by a physiotherapist.

## Methods/design

### Design

The effects of the task-oriented CCT programme will be investigated by means of a stratified, multicentre, single-blinded, randomized controlled trial (RCT) conducted by specially trained staff in nine selected rehabilitation centres in The Netherlands. Within each participating rehabilitation centre, patients will be allocated to the task-oriented CCT (experimental group) or regular face-to-face physiotherapy (control group) for outpatient rehabilitation.

### Setting

The study will be conducted in nine rehabilitation centres in The Netherlands ('De Hoogstraat', Utrecht; 'Heliomare', Wijk aan Zee; 'Rijnlands Revalidatiecentrum', Leiden; 'Sophia Revalidatie', Den Haag; 'Stichting Revalidatie Breda', Breda; 'Via Reva/Kastanjehof', Apeldoorn; 'Roessingh', Enschede; 'De Trappenberg', Huizen and 'Vogellanden', Zwolle). All patients will complete an inpatient rehabilitation period and will be included when they start their outpatient rehabilitation period.

### Participants

Eligible subjects will have to meet the following inclusion criteria: (1) verified stroke according to the WHO definition[23], (2) ability to walk a minimum of 10 m without physical assistance from a therapist. (i.e., patient may require verbal supervision or stand-by help from a person, and using an aid or orthotics is allowed) (Functional Ambulation Categories ≥ 3); (3) discharged home from a rehabilitation centre; (4) need to continue physiotherapy during outpatient care to improve walking competency and/or physical condition; (5) giving informed consent and being motivated to participate in 24 fitness training sessions over a 12-week period, or in usual care. Patients will be excluded if they (1) suffer from severe cognitive deficits as evaluated by the Mini-Mental State Examination (<24 points); (2) are unable to communicate (i.e. < 4 points on the Utrechts Communicatie Onderzoek) or (3) live more than 30 km from the rehabilitation centre. Before discharge from an inpatient rehabilitation setting, patients will be recruited by their own physician, and after they have given written informed consent, an observer will verify if all inclusion criteria have been met to participate in the trial. The FIT-Stroke protocol has been approved by the Medical Ethics Committee of the University Medical Centre Utrecht and all the participating rehabilitation centres. The trial is registered in the Dutch Trial Register (NTR1534).

### Definitions used in FIT-Stroke

*Task-oriented circuit class training *is defined in the present study as therapy provided to at least 2 participants simultaneously, which involves a series of workstations focusing on gait practice and functional gait-related tasks. The workstations are organized as a circuit, and the exercise at each workstation has to be progressive, i.e., increasing the number of repetitions completed at a workstation and/or increasing the complexity of the exercise performed at each station[19]. Circuit class training allows staff-to-patient ratios to be lower than they are in individual physiotherapy and enables a group of patients to exercise at different workstations simultaneously under the supervision of one or more therapists[24].

*Walking competence *is defined as **'**the ability to perform gait and gait-related tasks successfully', with gait-related activities defined as activities involving mobility-related tasks such as stair walking, turning, making transfers, walking quickly and walking specified distances'[18]. *Independent gait *is defined as level three or higher according to the Functional Ambulation Categories (FAC). FAC 3 reflects that patients require verbal supervision or stand-by-help from one person without physical contact, whereas FAC 4 indicates that patients are safe walkers on level ground, but require help on stairs, slopes or uneven surfaces, and FAC 5 means that patients are able to walk independently anywhere[25,26].

The proposed study will determine *cost-effectiveness *by relating the costs to the effects of the programme. The effects will be expressed as quality-adjusted life years (QALYs) determined by the EQ5D. The costs include the costs related to resource use of primary care practitioners, secondary care appointments, admissions to health care facilities, community-based support and individual out-of-pocket expenditure (direct costs). Medication costs and costs related to devices and adaptations in and around the house will also be included. The costs of productivity losses (indirect costs) will not be included in the analysis. The incremental cost-effectiveness ratio (ICER) will be determined by dividing the mean difference in costs by the mean difference in effect between the two groups.

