### Procedure

Patients will be stratified by rehabilitation centre and subsequently randomized to task-oriented CCT or to individual face-to-face physiotherapy, using an 'online' minimization procedure[27]. The intervention period will be 12 weeks and measurements will be taken at baseline, 6, 12, 18 and 24 weeks. All outcomes measured at baseline, 12 and 24 weeks will be assessed in face-to-face meetings by an independent researcher, blinded for treatment allocation, whereas at 6 and 18 weeks, a restricted set from the test battery will be assessed by semi-structured telephone interviews (Figure 1).

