#### EuroQoL

The EuroQol is a generic measure of quality of life (QoL) and consists of a health status profile in five domains (EQ-5D), including two that are directly related to mobility[36]. It also includes a visual analogue scale (VAS) reflecting patients' overall judgement about their current health status. The EuroQol has been validated for use in stroke[37,38]. The advantage of the EuroQol is that it can be transformed into a utility score based on patients' VAS scores and population estimates of the health-status profile, allowing cost-effectiveness assessment. The VAS score will be used to detect possible overall effects of the training programme, compared to usual care, that were not specifically targeted by the intervention programme. For short-term effects, the EuroQol will be assessed at baseline and 6, 12, 18 and 24 weeks after randomization.

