### Data analysis

The present trial, with repeated measurements nested in each patient, will apply a random coefficients model (MLWIN, version 2.11) to evaluate differences in effect between the experimental and control intervention arms. Besides the type of intervention, the model will include significant factors such as covariates, which will be established by means of (univariate) regression analysis. It should be noted that Random Coefficient Analysis (RCA) is able to deal with (partially) or completely missing values and enables an 'intention-to-treat' analysis. Economic evaluation will be conducted from the main assumption underlying the present study, that the proposed fitness training programme, which allows stroke patients to train in groups of 8 to 10, will result in a better walking competency as well as improved (I)ADL and HRQoL, with net savings on resources (i.e., costs), compared to the control intervention. The balance between costs and effects will be estimated, in accordance with the Dutch guidelines for pharmaco-economic research, by means of multivariable probabilistic data analysis [56]. The cost diary will comprise detailed questions on items such as consultations with neurologists, family doctors, paramedics, home care and non-professional support, and the answers will be used in the costs evaluation. Provision of medication by pharmacies in the community will also be recorded to keep track of expenses related to drug use. The diary will also record low volumes of high-cost resources, such as re-admission to hospitals and rehabilitation centres. Ultimately, multiplication of resource use and unit costs, which will be determined in a separate cost study, will yield an estimate of patient-level cost. Subsequently, summation across individual patient records and averaging will yield an estimate of total costs per intervention arm. In addition, the impact of task-oriented CCT in terms of health-related quality of life will be determined using the EuroQol 5D (EQ-5D). The EQ-5D is a 5-item questionnaire that can be converted into a single value score (i.e., utility) for HRQoL, yielding an estimate of the quality-adjusted survival time (QALYs). This estimate will serve as the primary measure of effectiveness for the economic evaluation.

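### The ICER's QALY difference is defined without a stated adjustment for the baseline EQ-5D utility that the trial collects, which lets chance imbalance into the denominator and gives up precision

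*Protocol article*

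**What the plan says.** The section Definitions used in FIT-Stroke sets the effect measure, "The effects will be expressed as quality-adjusted life years (QALYs) determined by the EQ5D", and says that the ICER is "determined by dividing the mean difference in costs by the mean difference in effect between the two groups". The Data analysis section builds the cost side from patient-level resource use and unit costs, after which "summation across individual patient records and averaging will yield an estimate of total costs per intervention arm". Of the QALY it says: "This estimate will serve as the primary measure of effectiveness for the economic evaluation". The balance of costs and effects is to be estimated "by means of multivariable probabilistic data analysis", and the article does not say what that analysis contains.

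The EuroQoL section confirms that a baseline value exists: "the EuroQol will be assessed at baseline and 6, 12, 18 and 24 weeks after randomization". On allocation, the Procedure section states: "Patients will be stratified by rehabilitation centre and subsequently randomized to task-oriented CCT or to individual face-to-face physiotherapy", by online minimisation. Centre is the only factor named.

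Covariates are mentioned once, in Data analysis, for the random coefficients model. They are to be those found significant in univariate regression.

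**The concern.** Baseline utility is the starting point of each patient's 24-week utility curve and is normally correlated with every later point. A difference in arm means that ignores it therefore contains a share of whatever baseline difference chance has produced. It also leaves in the QALY variance a component that a regression would remove.

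This matters because cost-effectiveness is one of the trial's two key aims and the QALY is its effect measure. Over 24 weeks the attainable QALY difference is small, and it is the denominator of a ratio, so a small shift can move the ICER a good deal. The sample size was set for SIS mobility only, so no stated precision protects the QALY comparison.

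**Working it through.** **The plan's own figure.** The article gives no precision figure for QALYs, EQ-5D or the ICER. Its sample size concerns SIS mobility and can be reproduced, assuming a two-sided 5% level: 2 × 14² × (1.96 + 0.84)² / 5² = 123.1 per arm. Multiplying by the stated ICC of 0.8 gives 98.5, rounded up to 99, and 198 / 0.9 = 220. The only part used below is the 99 per arm.

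**Inputs from the article.** EQ-5D at 0, 6, 12, 18 and 24 weeks; 99 evaluable patients per arm.

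**Assumptions, because the article gives no figures.** The QALY is the trapezoidal area under the utility curve. Variances are equal across visits. The utility SD is 0.25 (range 0.20 to 0.30). The correlation between visits is either equal for all pairs (rho) or first-order autoregressive. Imbalance is that of simple randomisation.

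**Formulas.** With equal spacing, the weights on the five visits are 1/8, 1/4, 1/4, 1/4, 1/8. Let c be the covariance of mean 24-week utility with baseline, and V the variance of mean 24-week utility, both in units of the utility variance.

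- Under equal correlation, c = 1/8 + (7/8)rho and V = 7/32 + (25/32)rho.
- c is the share of a baseline difference that carries into the unadjusted mean utility.
- c²/V is the share of QALY variance removed by adjusting for baseline.
- √(1 − c²/V) is the ratio of adjusted to unadjusted standard error.

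| Correlation structure | c | V | Variance removed | SE ratio |
|---|---|---|---|---|
| Equal, 0.3 | 0.39 | 0.453 | 33% | 0.82 |
| Equal, 0.5 | 0.56 | 0.609 | 52% | 0.69 |
| Equal, 0.8 | 0.83 | 0.844 | 81% | 0.44 |
| Autoregressive, adjacent 0.5 | 0.35 | 0.486 | 25% | 0.86 |
| Autoregressive, adjacent 0.7 | 0.54 | 0.654 | 44% | 0.75 |
| Autoregressive, adjacent 0.8 | 0.66 | 0.756 | 58% | 0.65 |

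Weaker correlation gives less: 15% for autoregressive with adjacent 0.3.

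**Size of an ordinary imbalance.** One standard error of the baseline difference is 0.25 × √(2/99) = 0.0355. Its effect on the QALY difference is c × 0.0355 × 24/52, which is 0.0064, 0.0092 and 0.0135 for equal correlation of 0.3, 0.5 and 0.8. Over SDs of 0.20 to 0.30 the range is 0.0051 to 0.0162.

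**A yardstick.** A utility gain of 0.05 (an assumed value) held at all four follow-up visits is worth 0.05 × 7/8 × 24/52 = 0.0202 QALY. At rho 0.5, the one-SE shift is 0.0092 / 0.0202 = 46% of that. With the cost difference held fixed, the ICER would be multiplied by 0.0202 / (0.0202 + 0.0092) = 0.69 or by 0.0202 / (0.0202 − 0.0092) = 1.84, depending on the direction of the imbalance.

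**The case against.** The strongest reply is that the article never calls the difference raw or unadjusted. The ICER sentence is the ordinary definition and would also fit regression-adjusted differences. The phrase "by means of multivariable probabilistic data analysis" leaves room for adjustment, and a condensed article may leave covariates to a fuller plan. The cost sentence describes how arm totals are built, not necessarily how the increment is estimated. EuroQol is also a primary outcome, so the random coefficients model might be meant to supply the effect difference. Finally, the minimisation factors are not fully listed, so the true imbalance could be smaller than under simple randomisation.

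Much of this stands, and it limits the claim: a reader might infer that the plan prescribes an unadjusted analysis, and the text does not say so. It does not remove the point. The article gives a formula for the ICER and an averaging step for costs, and following both as written involves no baseline utility. The one covariate rule is attached to another model. Even if that rule were extended to QALYs, selection by univariate significance would not guarantee that baseline utility enters.

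**Conclusion.** The point holds as a recommendation to specify a better estimator. On the plain reading, part of a chance baseline imbalance enters the QALY difference (0.39 to 0.83 of it for equal correlation of 0.3 to 0.8), and roughly 25% to 80% of the QALY variance could be removed by adjustment, depending on a correlation the documents do not give.

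Four stronger readings are tempting and not supported:

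- **Bias.** Randomisation keeps the unadjusted difference unbiased on average. The issue is chance imbalance and efficiency.
- **Full carry-over.** It is partial in every case calculated.
- **Loss of most of the precision.** On the variance scale this needs an equal correlation of about 0.5 or more, or an adjacent-visit autoregressive correlation of about 0.75 or more. On the standard-error scale, a reduction of more than half needs about 0.75 under equal correlation. The article's 0.8 is a test-retest figure for the SIS and cannot be borrowed for the EQ-5D.
- **A matching gain for costs.** The variance figures concern QALYs only. No gain has been shown from adjusting costs, or from adding centre, and the uncertainty of the ICER also depends on the cost difference.

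**What to change.** In Definitions used in FIT-Stroke and in the economic part of Data analysis, define the incremental QALY as the arm coefficient from a patient-level regression of the 24-week QALY on arm, baseline EQ-5D utility and rehabilitation centre. Name these covariates in advance, whatever their univariate significance. Carry the adjusted difference through the probabilistic analysis jointly with the cost difference, for example by resampling patients and re-estimating both in each bootstrap sample. Adjusting costs for centre is optional and secondary.

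If this is already intended, a sentence saying so is enough. Otherwise the cost is a change of wording and one regression inside the resampling, with no new data and no more patients. The ICER will no longer equal the ratio of the unadjusted arm-mean differences, so tabulate the arm means as description and state which estimate the ICER uses.
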